### Variables

#### Quantitative Variables

A variety of factors with potential influence on the diagnostic process will be extracted from both the EHR and other standalone databases at the 2 sites. Existing literature has provided information on factors related to patients, providers, and system-level parameters and the interactions of these parameters in the ED (eg, patient-per-provider ratio and patient length of stay), which can be explored further [8,13,24-29]. Several additional variables that can be extracted from the EHR will be under consideration. The number of unexpected ED visits could be associated with a higher risk of diagnostic error [8,25]. ED crowding is a complex issue related to both system-level and patient-level factors (complexity and acuity) [28] and is associated with an increased risk for patient safety, including treatment delays, reduced quality of care, and increased morbidity and mortality [24]. Prolonged ED length of stay correlates with increased patient mortality [27]. High workloads, lack of control, and communication failures may lead to patient safety risks [29]. Iordache et al [30] showed that direct and indirect care time together are significant discriminators between EDs because of the differences between their patient care profiles and unit characteristics. Prescribing error rates are shown to significantly increase if physicians are interrupted or are multitasking [31]. Textbox 1 provides a general overview of these 3 categories.

The three main categories of risk factors to be explored in this study.

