### Conduct of the Study

#### Overview

This study aims to identify the factors that may interfere with the diagnostic process in the ED that potentially lead to missed, delayed, or incorrect diagnoses. On the basis of our previous work, we will use a series of electronic triggers (triggers) to identify ED encounters with potential diagnostic errors from the EHR database. Each trigger has a predefined set of inclusion and exclusion criteria implemented in Structured Query Language (SQL) and configured for specifications of each site in the study. Each site currently uses an Epic EHR system with minimal variations owing to its specific needs. These differences will be identified and accounted for after the focus interviews with the providers. The Epic specialists at both sites are in constant communication with the research team to apply the most accurate mapping of the factors and parameters between the 2 sites. The protocol is thought to be generalizable to other EHR systems, as we emphasize the analysis of common ED concepts rather than database variables specific to Epic. All SQL queries can be modified to match other systems (eg, Cerner) by matching concepts and keywords. Table 1 provides an initial list of 6 EHR-based triggers proposed in IDEA-LL after reviewing the literature on current triggers, surveying medical directors, and using a Delphi consensus process [32]. We will start our study with the first 3 triggers, including the unscheduled visit within 10 days resulting in admission, care escalation to intensive care unit within 24 hours, or death in the ED or within 24 hours of ED departure time. If for any reason, one or more of the triggers do not perform well, the triggers from the backup set will be used.

**Table 1 table1:** Proposed electronic trigger algorithms for identifying diagnostic errors.

Trigger algorithm			Description

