**Initial set of triggers**			
	Trigger 1: unscheduled return	Unscheduled return visit with admission within 7 to 10 days from the index ED^a^ visit.	
	Trigger 2: care escalation	Care escalation from the inpatient unit to the ICU^b^ within 6, 12, or 24 hours with ED attribution.	
	Trigger 3: death	All deaths in the ED or within 24 hours of admission—exclusive of palliative care.	

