#### Step 1: Sampling of Trigger-Positive and Trigger-Negative Charts

This step will apply the EHR-based trigger algorithms (Table 1) to the EHR data repositories that include ED encounters at the 2 sites, creating large data sets of statistically matched groups (for demographics and medical comorbidity or severity) for trigger-positive and trigger-negative (control) charts [36]. The inclusion and exclusion criteria for individual triggers will be refined after an iterative review of random samples of charts. We anticipate using 3 triggers that have the best predictive value for diagnostic errors.

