**Trigger 3: Specific Factors**
ED discharge (D/T)ED dispositionED departure (D/T)ED unitDischarge-to-death (hours)Hospital disposition

We have also updated the SQL queries of all 3 triggers to be compatible with the EHR databases at both sites. ED patients’ evaluations against each trigger are performed upon the execution of these queries on each EHR database. We reinforced multiple inclusion and exclusion criteria to the queries to ensure that test data or irrelevant information do not affect our selections. All queries share common information related to the initial encounter, followed by specific factors collected for each trigger separately. Figure 4 shows an example relational database schema on how different factors are being invoked and matched from multiple database tables to identify encounters with an escalation in the care condition, denoted by trigger 2.

The outcomes of this project include an improved understanding of the risk factors contributing to diagnostic error in the ED. The data could be used to inform EHR-based decision support systems for better prediction of the risk of diagnostic error in the ED. The first exploratory results of the project are expected to be submitted for publication by mid-2021.

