### Limitations and Strengths

We anticipate some difficulties and potential limitations to our forthcoming project. First, although we have based our analysis on the patients’ medical records, it is notable that this information is not always available at all sites. Our method potentially cannot be extended to EDs that do not have an integrated EHR system, as different EDs might use incompatible EHR systems to ours, which at least requires an adaptation phase. We intentionally chose the community and academic sites to learn more about the potential difference and have recruited clinicians at each site to determine important differences and help customize the trigger algorithms. We also believe that by incorporating commonly accepted and standard measurements in this study, any future translation to other health systems would be possible by a simple mapping to the database elements of the target EHR system.

Second, our approach to investigate the risk of diagnostic error for ED patients with care escalation or death within a certain period from ED discharge will not include many events, including those that occur within the same ED encounter, possible events in other hospitals, and flag records that meet trigger criteria but are not associated with diagnostic error. We will attempt to update our data exploration approach to reduce the rate of such false-positive triggers. Conversely, a strength of our study is that the simultaneous investigation of 2 separate health systems with both adult and pediatric EDs reduces the chance of biased conclusions. These limitations are balanced by several unique strengths of this study to help identify potentially associated contributory factors of diagnostic error in the ED.

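### Deaths in the ED cut short the whole-stay predictors used for Trigger 3, and the article disagrees with itself on whether those deaths count and which 24-hour clock applies

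*Protocol article*

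**What the plan says.** Trigger 3 is described in three places in the protocol article.

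- **Table 1, initial set of triggers:** "All deaths in the ED or within 24 hours of admission—exclusive of palliative care".
- **Conduct of the Study, Overview:** "death in the ED or within 24 hours of ED departure time". The palliative exclusion is not repeated here.
- **Limitations and Strengths:** the approach based on "care escalation or death within a certain period from ED discharge will not include many events, including those that occur within the same ED encounter".

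Textbox 2 in Results lists potential predictors taken from the EHR. Those common to all triggers include "ED length of stay" and the number of laboratory tests.

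Step 4 applies association rule mining, CHAID and CART with the trigger label as the outcome. The CHAID section takes a combination of factors that raises the chance of a positive trigger to raise the relative risk of diagnostic error as well.

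Controls are encounters that meet no trigger. They are matched on age group, gender, provider, reason for visit and arrival date and time (Sampling for Control), and on demographics and comorbidity or severity (Step 1).

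**The concern.** A predictor should be fixed before the outcome, or at least not be determined by it. When a patient dies in the ED, the death sets the Trigger 3 label, and it also ends the stay and stops further testing. Length of stay and test count then partly record the outcome itself.

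Tree and rule methods split on whatever separates the labels. They cannot tell a stay that was short because the work-up was hurried from one that was short because the patient died. If the second kind drives a split, the study could report hurried evaluation as a risk factor for diagnostic error when the data show only that death ends a visit. The article intends its findings to inform later causal work and decision support, so such an artefact would be carried forward.

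The conflicting descriptions add a second problem. A reader cannot tell whether deaths in the ED are in the case group at all, or which deaths after the ED are.

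**Working it through.** No figure in the article can be recomputed. It gives no number of deaths, no share of deaths occurring in the ED and no lengths of stay. The check is therefore a comparison of the passages plus one line of algebra.

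**1. Do deaths in the ED count?** Table 1 and the Overview both say yes. The Limitations sentence describes death after ED discharge and says events within the same encounter are not included. Read plainly, that leaves out a death in the ED.

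**2. Which clock applies?** Table 1 counts from admission, the Overview from ED departure, and the Limitations section refers to ED discharge. The choice changes who is a case:

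- A patient sent home who dies within 24 hours of leaving is a case under the Overview. Under Table 1 that patient is not a case, because there was no admission (taking admission to mean hospital admission).
- A boarded patient, whom the article describes as admitted but still in the ED, starts the admission clock before the departure clock. A death can then fall outside 24 hours from admission but inside 24 hours from departure.

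**3. Which predictors are affected?** ED length of stay runs from arrival to the end of the ED visit, and the test count accumulates over that time. For a death in the ED both stop at death. For a death after departure the ED stay is complete, so only the in-ED subgroup is affected.

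**4. Does matching remove the effect?** Age group, gender, provider, reason for visit, arrival time, demographics and comorbidity or severity are all properties of the patient or the arrival. None makes a control's stay end early. Suppose cases and controls would have had the same mean stay had nobody died in the ED. Let s be the share of Trigger 3 cases who died in the ED, and d the mean ED time lost to death among them. Then

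mean stay in cases − mean stay in controls = −s × d.

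This is negative whenever s and d are above zero, even if no factor is related to diagnostic error. The same holds for the test count, with d as the mean number of tests not done. The article gives neither s nor d, so only the sign follows.

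**5. How would the result be read?** Through the CHAID section's link from trigger-positive risk to error risk, a split on short stay or few tests would be reported as a marker of diagnostic error.

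**6. The palliative exclusion.** Table 1 does not say when palliative status must have been recorded. If only status before or at arrival counts, a patient moved to comfort care after deteriorating remains a case. If later status also counts, that death is removed and, if it meets no other trigger, becomes eligible as a control. The article fixes neither reading.

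**The case against.** The strongest reply is that Table 1 is a summary list of proposed triggers. The article says that each trigger has predefined criteria in site-configured SQL, which it does not reproduce. It adds "We reinforced multiple inclusion and exclusion criteria to the queries to ensure that test data or irrelevant information do not affect our selections" and "The inclusion and exclusion criteria for individual triggers will be refined after an iterative review of random samples of charts". How palliative care is coded and timed, and how arrivals in cardiac arrest are handled, may well be settled there. This stands. It is why the palliative timing is raised only as a clarification and the absence of a rule for arrest arrivals is not raised as a fault.

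A second reply is that false positives are acknowledged: the triggers will "flag records that meet trigger criteria but are not associated with diagnostic error". Chart review with the Revised Safer Dx, selection on predictive value and a backup set of triggers are all planned. That answers a complaint about predictive value, but it does not reach the predictor problem. Even if every death in the ED followed a diagnostic error, length of stay and test count would still be cut short by the death.

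A third reply is that Textbox 2 lists potential predictors rather than a final model, and that the Limitations sentence may mean diagnostic events that arise and resolve within one visit. Both are fair. The first makes the artefact a possibility rather than a certainty, and the second makes the conflict one of wording that an edit can settle. Neither explains the two different 24-hour clocks.

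A reader might go further and infer that Trigger 3 drops missed diagnoses moved to comfort care. The text does not support that, because it holds only if status assigned after arrival counts, and no passage says so. A reader might also infer that a large part of the trigger's predictive value is lost to patients who arrive in arrest. The article gives no figure from which a loss could be computed, and patients already under palliative care are excluded on either reading.

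**Conclusion.** Two points hold on the text as printed.

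First, Trigger 3 as defined in Table 1 and the Overview includes deaths in the ED, while Textbox 2 offers predictors that those deaths cut short. Neither the matching nor the stated safeguards removes this. The direction is towards shorter stays and fewer tests among cases. The size depends on the share of Trigger 3 cases who die in the ED and the ED time lost to death, and the article reports neither. The point assumes that the labelled cohort does contain deaths in the ED and that these two variables are used in Step 4 as listed.

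Second, the descriptions of Trigger 3 disagree on whether deaths in the ED count and on when the 24 hours begin.

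The timing of the palliative exclusion is a secondary ambiguity. It is a question to answer, not a demonstrated bias.

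**What to change.** 1. **Reconcile the definition first.** Make Table 1, the Overview and the Limitations section agree on whether deaths in the ED count and on one starting point for the 24 hours. Results says the cohort is already labelled by scripts, so the operative rule can be read from the code. If deaths in the ED turn out not to count, steps 2 and 3 are not needed.
2. **Split the label.** Analyse deaths in the ED (3a) separately from deaths after ED departure (3b). Assign boarded patients by whether they had physically left the ED, because a death while boarding also cuts the ED stay short.
3. **Restrict predictors in 3a.** For 3a and its matched controls, use only variables fixed at arrival or triage, such as demographics, visit history, comorbidity, chief complaint, arrival time, triage severity and ED crowding at arrival. Leave out length of stay, test counts and other items known only at the end of the visit. They can remain in 3b, where the ED stay is complete.
4. **State the palliative timing.** Say whether the exclusion is limited to status documented before or at ED arrival, and whether a death removed by it can serve as a control.

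A blanket exclusion of patients arriving in arrest is not part of this fix. It could discard a patient who was sent home and returned in arrest, which is a plausible missed diagnosis.

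The work is text edits and query edits. The price is fewer cases in each Trigger 3 stratum, and in 3a the loss of any information that length of stay and testing would have carried.

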**Backup set of triggers**			
	Trigger 4: change of service	A proxy for the discrepancy in diagnosis may be the change of service in 48 hours (admitted medical, changed to surgical).	
	Trigger 5: nonadmitted returns	Return visits not resulting in admission with new interventions (eg, diagnostic test that was abnormal, new medication).	
	Trigger 6: high-risk conditions	New diagnosis or symptom-disease dyads (eg dizziness-stroke [33] and abdominal pain-appendicitis [34]).	

^a^ED: emergency department.

^b^ICU: intensive care unit.

We will perform a retrospective review of a selected sample of both trigger-positive and trigger-negative medical records to identify the presence or absence of diagnostic errors using the Revised Safer Dx, a validated instrument for categorizing the presence of diagnostic errors [35]. We will then compare these 2 large cohorts to evaluate associations of potential contributing factors with trigger-positive cohorts using sophisticated data mining techniques. To conduct this study, we will accomplish the following 4 steps.

#### Step 1: Sampling of Trigger-Positive and Trigger-Negative Charts

This step will apply the EHR-based trigger algorithms (Table 1) to the EHR data repositories that include ED encounters at the 2 sites, creating large data sets of statistically matched groups (for demographics and medical comorbidity or severity) for trigger-positive and trigger-negative (control) charts [36]. The inclusion and exclusion criteria for individual triggers will be refined after an iterative review of random samples of charts. We anticipate using 3 triggers that have the best predictive value for diagnostic errors.

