## Abstract

**Background:**

Diagnostic decision making, especially in emergency departments, is a highly complex cognitive process that involves uncertainty and susceptibility to errors. A combination of factors, including patient factors (eg, history, behaviors, complexity, and comorbidity), provider-care team factors (eg, cognitive load and information gathering and synthesis), and system factors (eg, health information technology, crowding, shift-based work, and interruptions) may contribute to diagnostic errors. Using electronic triggers to identify records of patients with certain patterns of care, such as escalation of care, has been useful to screen for diagnostic errors. Once errors are identified, sophisticated data analytics and machine learning techniques can be applied to existing electronic health record (EHR) data sets to shed light on potential risk factors influencing diagnostic decision making.

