#### Sampling for Control

The control includes visits that do not meet the criteria for any trigger. We will include all ED visits in the two health systems for the entire study period (July 1, 2017-December 31, 2019). For each trigger-positive case, we will match a single trigger-negative encounter based on the availability of cases through a hierarchical procedure, which matches the encounters based on age group, gender, provider, the reason for visit, and the arrival date and time. This one-to-one matching of trigger-positive and trigger-negative cases will also help to eliminate the imbalance classes. To accommodate the potential heterogeneity across sites, the measurements will be reported as site-specific quartiles [24]. For patients with multiple ED or hospital visits during the study period, each record will be considered separately.

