**Patient Factors**
DemographicsEmergency department (ED) visit historyComplexity and comorbidity

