**Provider-Care Team Factors**
Shift schedule and workloadPatient-per-provider ratioInterruptions and trauma

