**System Factors**
ED boardingEmergency severity index triage distributionTotal direct and indirect care time

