#### Qualitative Variables

Qualitative analysis of the ED environments, such as the cognitive load on individual providers, is outside the focus of this study but is under exploration in another aim of this grant. However, we will study factors such as patient acuity, patient volume, waiting times, number of ED providers per shift, and number of boarded ED patients (admitted to inpatient unit but still in ED because of lack of inpatient space) in the system as proxies for some of the qualitative factors such as the cognitive load.

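### Two unreconciled matching lists define the same control group, and the one followed decides which risk factors can show a main-effect association with trigger status

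*Protocol article*

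**What the plan says.** Methods, Sampling for Control, sets the ratio and the variables: "For each trigger-positive case, we will match a single trigger-negative encounter", by a hierarchical procedure, subject to availability, that "matches the encounters based on age group, gender, provider, the reason for visit, and the arrival date and time". Comorbidity and severity are not on that list.

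Methods, Step 1, describes the same trigger-positive and trigger-negative charts as the product of "creating large data sets of statistically matched groups (for demographics and medical comorbidity or severity". Provider, presenting reason and arrival timing are not on that list.

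The Abstract (Methods) says that the relationships between risk factors and diagnostic safety signals will be evaluated in the statistically matched groups. The factors to be examined include:

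- Textbox 1, Patient Factors: "DemographicsEmergency department (ED) visit historyComplexity and comorbidity" (three entries run together in the extracted text).
- Textbox 1, Provider-Care Team Factors: "Shift schedule and workloadPatient-per-provider ratioInterruptions and trauma".
- Textbox 1, System Factors: "ED boardingEmergency severity index triage distributionTotal direct and indirect care time".
- Qualitative Variables: "we will study factors such as patient acuity, patient volume, waiting times, number of ED providers per shift", together with the number of boarded patients.

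Textbox 2 adds ED length of stay and the number of laboratory tests as candidate predictors for all triggers.

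**The concern.** A variable used for matching has its marginal association with case status removed by the design. The matching list is therefore also a list of what the study cannot detect as a main effect. With two lists that agree only on demographics, two analysts each following one section would draw different controls and could produce different risk factor lists from the same records.

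The study is exploratory, but its output is meant to be used: the Objective section says that it will inform aim 2 and the design of decision support. The initial triggers are return with admission, escalation to intensive care, and death, all plausibly related to how ill the patient was on arrival. Whether severity is matched, adjusted for or left free therefore affects how length of stay, test counts and similar candidates are interpreted. The odds ratios for diagnostic error in Step 2 also depend on which controls are drawn.

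**Working it through.** The document gives no sample size, event count or effect size for this comparison, so there is no figure of its own to reproduce. The check has two parts.

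**1. The lists side by side.**

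| Variable | Sampling for Control | Step 1 | Named study factor it bears on |
|---|---|---|---|
| Age, gender | matched | matched (demographics) | Demographics |
| Provider | matched | not named | Shift, workload, patient-per-provider ratio |
| Presenting reason | matched | not named | Chief complaint (Textbox 2) |
| Arrival date and time | matched | not named | Shift, crowding, waiting, boarding |
| Comorbidity or patient severity | not named | matched (one or the other) | Complexity and comorbidity; possibly acuity |

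Only the first row agrees. No sentence makes one list a stage or a summary of the other. Each rule also matches on variables that are study factors or that largely determine them.

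**2. Illustration of the consequence.** All inputs here are assumptions, not figures from the protocol:

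- 600,000 encounters and 1:1 exact matching without replacement.
- 20 equally likely arrival slots, with crowding fully fixed by slot (10 crowded, 10 not).
- 10 complaint groups, with severity prevalence rising from 15% to 42% across them.
- Trigger status from a logistic model with a crowding odds ratio of 1.5 and a severity odds ratio of 1.5, 2, 3 or 5.
- Provider, age and gender not simulated.

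The Sampling for Control rule is represented by matching on complaint and slot, and the Step 1 rule by matching on severity. The odds ratio is [p1/(1−p1)]/[p0/(1−p0)], where p1 and p0 are the proportions with the factor in trigger-positive and trigger-negative encounters.

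| True severity OR | Complaint + slot: severe, case v control | Severity OR | Crowding OR | Severity-matched: severe, case v control | Severity OR | Crowding OR |
|---|---|---|---|---|---|---|
| 1.5 | 37.4% v 28.4% | 1.50 | 1.00 | 37.4% v 37.4% | 1.00 | 1.54 |
| 2 | 43.3% v 27.7% | 2.00 | 1.00 | 43.3% v 43.3% | 1.00 | 1.47 |
| 3 | 53.7% v 28.8% | 2.86 | 1.00 | 53.7% v 53.7% | 1.00 | 1.48 |
| 5 | 65.2% v 28.4% | 4.72 | 1.00 | 65.2% v 65.2% | 1.00 | 1.51 |

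Worked for the last row: (0.652/0.348)/(0.284/0.716) = 1.874/0.397 = 4.72 under complaint and slot matching. Under severity matching p1 = p0, so the odds ratio is 1 whatever the true value.

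The 1.00 entries follow from matching exactly on the factor or on what fixes it. In the actual study, crowding would be removed fully only if arrival date and time were matched closely; looser matching would weaken it instead.

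**The case against.** The strongest defence is that Sampling for Control is the operative section and the Step 1 clause is a parenthesis in a summary, with a citation, in an article that condenses a fuller protocol. Condensation excuses missing detail. It does not turn comorbidity or severity into shorthand for provider, presenting reason and arrival time. The conflict between two stated lists stands, although one may have been intended as the rule.

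Several stronger readings are tempting, and the documents do not support them:

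- A reader might infer that Step 1 equalises both comorbidity and acuity. The wording offers one or the other, so the unmatched one can still vary.
- A reader might infer that the triage index in Textbox 1 is neutralised as well. It is listed as a system factor, and Step 3 describes it as the severity of ED workload. Matching two patients on their own severity does not equalise the department's triage mix. Patient acuity is likewise named mainly as a proxy for cognitive load. Complexity and comorbidity is the one factor clearly affected at patient level.
- A reader might infer that a matched factor cannot appear at all. Matching removes the main effect, not effect modification. The rules and trees look for combinations, so a matched variable can still enter a lower split or a multi-factor rule.
- A reader might infer that trigger-positive patients must remain sicker under Sampling for Control. That is likely but not certain: age group and presenting reason may balance severity in part, and it can be handled in the analysis.
- A reader might treat the contrast between a severity odds ratio well above 1 and one of 1.00 as the size of a bias. It measures the difference between two designs. Leaving severity unmatched is also what allows it to be studied.

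Nor does the article say that a null result for a matched factor would be reported as no association. That is a risk to guard against, not something the plan states.

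**Conclusion.** The contradiction holds: one control group, two matching lists, only demographics in common, and no reconciliation.

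Under Step 1 the marginal effect of comorbidity or patient severity, whichever is matched, is removed by design although complexity and comorbidity is under study. Under Sampling for Control severity is not controlled by design, so candidates linked to it, such as length of stay and test counts, may separate the groups without bearing on diagnosis. That rule also removes or weakens the shift, workload, patient-per-provider, crowding and boarding factors. Matching on age and gender does the same to demographics under either rule. Choosing one existing list over the other therefore does not settle the matter.

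The size cannot be derived from the document. The simulation shows direction and mechanism only; it rests on the assumed odds ratios, exact matching, and crowding fixed by arrival slot. The point should be corrected because it changes what the study can conclude, but the work is hypothesis-generating and the remedy is cheap.

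**What to change.** 1. State one matching list, identically, in Sampling for Control and in Step 1, and use the resulting control set throughout.
2. Do not match on a variable that the study intends to assess as a risk factor. In particular, drop comorbidity or severity from the Step 1 matching. Enter comorbidity and patient-level triage severity, both measured at arrival, as inputs in Step 4, with adjustment or stratification for severity. Apply the same test to provider, arrival date and time, age group and gender before keeping them.
3. Declare that every variable kept in the matching, and every factor largely fixed by it (such as crowding and shift when arrival date and time are matched), cannot be assessed as a main-effect risk factor. Its absence from the association rule, CHAID or CART results should then not be read as no association.

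The cost is wording in two sections, a declaration, and an adjusted or stratified analysis. Textbox 2 lists neither comorbidity nor a patient-level triage score, so their extraction should be specified. The downside is smaller cells within severity strata and a shorter list of assessable factors. The Results section describes the cohort as labelled and the data as being cleaned, and reports no completed matching, so the change appears still possible.
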